### Process evaluation

In determining the usability and the facilitators and barriers to both the KONTAKT© and Super Chef programmes, and the factors likely impacting their efficacy, a process evaluation will be undertaken. Parents, adolescence, and trainers’ feedback on both programmes will be sought via semi-structured interviews at the completion of the programmes. This will provide an in-depth understanding of those factors influencing the relative efficacy of both the KONTAKT© and Super Chef programmes.

### Statistical analyses

As suggested by previous research, reliability of the GAS goals will be investigated via examination of their measurability, equidistance, and difficulty [57]. A random effects regression model will be used to explore those factors associated with the raw data on the GAS scores (dependent variable), over the 9-month duration of the study. Independent variables for the model will be time, group (KONTAKT© versus Super Che’), age, IQ, gender, centre, and comorbidity as fixed effects, with follow up being the primary endpoint of the study. The random effect will be the participant’s ID number, thus accounting for the correlation between measurements made on the same individual within the model.

Analysis of secondary outcomes (interpersonal efficacy, quality of life, social anxiety, loneliness, facial emotion recognition, and eye-tracking behaviour) will be conducted in a similar manner (random effects regression model). Analysis will be based on an intent-to-treat approach [84], considering each participant as belonging to the study group they were initially allocated, regardless of treatment actually received. Missing data will be accounted for according to the guidelines specified for each measure; if no guidance is provided, missing data will be handled in accordance with the CONSORT statement for conducting high-quality RCTs [48]. Data analysis will be conducted using the SPSS version 24 statistical software [88].

The outcomes of the present study will be compared to results obtained by previous evaluations of the short and long variant of KONTAKT© undertaken in Sweden.

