### Design

This will be a stratified (gender, site), RCT of a the SSGT programme (KONTAKT©) compared to a manualised active control group (a cooking group “Super Chef”) with a ratio of 1:1, adhering to the CONSORT statement for conducting high-quality RCTs [48] (Fig. 1). Data collection will occur at three time points (1): at baseline, prior to randomization to intervention or control; (2) at post-test, immediately following the intervention period; and (3) at follow-up, 12 weeks following the intervention (primary endpoint).

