### Sample size calculations

The KONTAKT© study in Sweden (both 12-week and 24-week versions) employed the Social Responsive Scale - second edition (SRS-2) as the primary outcome measure. Based on an effect size of 0.54, derived from roughly averaging the effect size (ES) as measured by the SRS-2 from trials examining the efficacy of the long 24-session (ES = 0.76) and the short 12-session (ES = 0.32) versions of KONTAKT© at post-test, and applying multivariate analysis of variance (MANOVA) for repeated measures (within-between interactions) at the three time points (using the intent-to-treat approach), a minimum of 57 participants are required (as calculated by G*Power [53] with power of 0.95 at a conventional error probability (α = 5%)). However, unlike the Swedish study, the present study will employ the Goal Attainment Scaling (GAS) as the primary outcome. It has been argued that GAS has good reliability when used as an outcome measure with interventions for adolescents with ASD [54–56]. Further, unlike previous investigation of KONTAKT© [17, 32], the current study will compare this SSGT efficacy against an active control group, to control for exposure to a social context with peers with ASD. It is likely that both these factors will have a limiting impact on the power of the study, and as such we will aim to recruit a sample of at least 90 participants into this study, increasing the likelihood of detecting possible effects [19]. This sample size will also account for an attrition rate of 37%, which is larger than what is expected based on the previous KONTAKT© studies.

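### Secondary outcomes: the stated model neither adjusts for the pre-randomization score nor sets a common baseline mean, which costs precision but not validity

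*Protocol article*

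**What the plan says.** Statistical analyses sets out a random effects regression for the GAS scores, run "over the 9-month duration of the study". The fixed effects are named: "Independent variables for the model will be time, group (KONTAKT© versus Super Che’), age, IQ, gender, centre, and comorbidity as fixed effects". The correlation within a person is handled as follows: "The random effect will be the participant’s ID number, thus accounting for the correlation between measurements made on the same individual within the model". For the secondary outcomes, the work "will be conducted in a similar manner (random effects regression model"). The outcomes named there are interpersonal efficacy, quality of life, social anxiety, loneliness, facial emotion recognition and eye-tracking behaviour.

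Design gives three data collection points. The first is "at baseline, prior to randomization to intervention or control" and the last is "at follow-up, 12 weeks following the intervention (primary endpoint"). Allocation is "with a ratio of 1:1".

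The only planning effect is in Sample size calculations: "Based on an effect size of 0.54, derived from roughly averaging the effect size (ES) as measured by the SRS-2". The article gives no correlation between baseline and follow-up scores and claims no power for any secondary outcome.

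**The concern.** The named fixed effects reach as far as age, IQ and comorbidity but leave out the participant's own score before randomization, which is usually the strongest predictor of the later score. Nor does the text say that the two arms share one mean at baseline, which randomization justifies.

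The primary outcome loses nothing by this. Under Primary outcome measure, −2 on GAS is defined as the current level of performance, so baseline is the same for everyone. The secondary scales do vary at baseline. For them the trial pays for a baseline measurement and then uses it less efficiently than it could. Intervals are wider than the data allow, and a real effect is more likely to be missed. The estimate also stays correlated with whatever chance difference between arms exists at baseline.

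**Working it through.** **The plan's own figure.** Sample size calculations gives a minimum of 57 for power 0.95 at α = 5%, using a repeated-measures MANOVA interaction with two groups and three times. Take 0.54 as the effect size f(V), with λ = N × 0.54², df1 = 2 and df2 = N − 3. Power is then 0.953 at N = 57 and 0.9497 at N = 56, so 57 reproduces. The attrition allowance also fits: 1 − 57/90 = 36.7%. Note that 0.54 works there as f(V), which is not the scale of a standardised mean difference. Using it as one below is an assumption.

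**Variances.** With n per arm, outcome SD 1 and correlation ρ between baseline and follow-up, the arm contrast at follow-up has variance (2/n) × factor:

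- baseline as a response, arms free at baseline, group-by-time contrast (change score): factor 2(1−ρ)
- baseline as covariate, or common baseline mean: factor 1−ρ²

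The ratio of the second to the first is (1+ρ)/2, so adjustment cuts the variance by (1−ρ)/2. At ρ = 0.5 that is 25%: 90 participants with adjustment are worth 90/0.75 = 120 without it.

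**Power.** Inputs: d = 0.54, n = 45 per arm, two-sided 5%, complete data, no clustering within training groups, other covariates ignored. Power = Φ(d / √(2/n × factor) − 1.96).

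At ρ = 0.5, √(2/45) = 0.2108.

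- Change score, factor 1: 0.54/0.2108 = 2.56, power 72.6%.
- Adjusted, factor 0.75: 0.54/(0.2108 × 0.866) = 2.96, power 84.1%.

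The noncentral t gives 71.7% and 83.3%.

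| ρ | Change score | Baseline-adjusted | Loss (points) |
|---|---|---|---|
| 0.3 | 58.1% | 76.6% | 18.5 |
| 0.5 | 72.6% | 84.1% | 11.5 |
| 0.6 | 81.7% | 89.3% | 7.6 |
| 0.7 | 91.1% | 94.8% | 3.7 |
| 0.8 | 98.2% | 99.0% | 0.8 |

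**Sensitivity.**

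- With 57 participants (28.5 per arm), the losses at the same values of ρ are 16.4, 12.2, 9.7, 6.5 and 2.8 points.
- At 45 per arm and ρ = 0.5, the loss is 8.9 points if d = 0.32 and 3.6 if d = 0.76. These are the two Swedish values that the plan averages.
- If the follow-up scores were compared with no use of baseline (factor 1), the loss at d = 0.54 and 45 per arm would be 4.0 points at ρ = 0.3, 11.5 at 0.5 and 22.2 at 0.7. The adjusted contrast beats this one too, since 1−ρ² is below 1.

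**Chance imbalance.** The covariance of a change score with baseline is ρ − 1, so its correlation with the baseline difference is −(1−ρ)/√(2(1−ρ)) = −√((1−ρ)/2). At ρ = 0.5 that is −0.5. The change score subtracts the raw imbalance but over-corrects for it. The adjusted contrast has correlation zero.

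**The case against.** The best defence is that the covariate list is written for GAS, where a baseline covariate would be constant and could not appear. Its absence there says little about what is intended elsewhere, and similarity of manner may mean only the same family of model. The article is also condensed, and detail for each outcome may sit in an analysis plan that is not shown. This lowers confidence about intent. Even so, the only model given is the one carried over to the secondary outcomes, and a colleague following the text would leave baseline adjustment out.

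Three stronger readings are tempting, and the article does not support them.

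- **That baseline is ignored, so chance imbalance passes straight into the result.** The model is longitudinal with a participant effect, and the sample size calculation refers to a within-between interaction. A change-type contrast is therefore the natural reading, and it subtracts the raw imbalance. What remains is over-correction and lower efficiency.
- **That a fixed 12 points of power are lost.** The figure is right only at ρ = 0.5 and d = 0.54. Neither is given for the six outcomes named, and SRS-2, the source of 0.54, is not in that list, although the article describes it as a secondary outcome.
- **That a baseline difference b shifts the group coefficient by b(1+2ρ)/3.** This holds only if the main-effect coefficient is reported with baseline among the responses. It follows from the separate absence of a named group-by-time term.

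It is also fair that both contrasts are unbiased under randomization and keep the type I error, and that no power is claimed for these outcomes.

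**Conclusion.** The point stands as one of efficiency. For secondary outcomes with a pre-randomization score, the stated model gives neither a baseline covariate nor a common baseline mean. The likely change contrast has variance 2(1−ρ) where 1−ρ² is available from the same data. At 90 participants and a standardised difference of 0.54, the loss runs from about 19 points of power at ρ = 0.3 to about 1 at ρ = 0.8. It is material for weakly to moderately correlated scales and negligible for highly correlated ones.

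This rests on an assumed ρ, on reading 0.54 as a standardised mean difference, on complete data and on no clustering. Inference under the plan would not be invalid, and the primary analysis is unaffected. The change is worth making because it is almost free.

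**What to change.** Add to Statistical analyses, before unblinding, one sentence covering each secondary outcome that has a pre-randomization score. The arm contrast at follow-up should come from a model with post-test and follow-up scores as outcomes, a group-by-time term, the baseline score as a covariate, and the other listed fixed effects kept. An equivalent alternative is a longitudinal model with baseline as a response and one baseline mean common to both arms.

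Leave out GAS, whose baseline is fixed at −2, and measures with no pre-randomization score: the experience sampling ratings, which start with the groups; the blinded expert video rating, first made at session 2; and the NEQ, completed at programme end. The contents of Table 3 are not shown, so the authors should check the list against it.

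The cost is the sentence and about one degree of freedom per outcome, with no new data, visits or participants. The covariate version drops anyone without a baseline score; the common-mean version keeps them.

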### Primary outcome measure

Goal Attainment Scaling (GAS) evaluates the outcomes and suitability of an intervention in an individual or group setting [58, 59]. Following the guidelines suggested by Kiresuk and colleagues (1994) adolescents randomized to both the treatment and control group, will establish at least three personally meaningful and measurable social goals in collaboration with an assessor blinded to the group allocation*.* The achievement of these goals will be scored via the GAS scoring system, whereby −2 indicates the participant’s current level of performance, −1 indicates less than expected, 0 indicates the expected progress, and +1 and +2 indicate progress above the expected level [60]. As suggested by previous research, the reliability of GAS will be calculated for this sample [54].

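### The primary model as listed has no group-by-time term, so it yields a visit-averaged arm difference and not the 12-week follow-up effect declared primary

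*Protocol article*

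**What the plan says.** Statistical analyses describes a random effects regression on "the raw data on the GAS scores (dependent variable), over the 9-month duration of the study". It then enumerates the terms: "Independent variables for the model will be time, group" (KONTAKT versus Super Chef), "age, IQ, gender, centre, and comorbidity as fixed effects, with follow up being the primary endpoint of the study". The list closes with "The random effect will be the participant’s ID number". Secondary outcomes are to be analysed in a similar manner.

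Three other statements bear on this list:

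- Design and Data collection both set three assessments (baseline before randomization, post-test, and 12 weeks after the intervention) and name the last as the primary endpoint.
- Sample size calculations obtains its minimum of 57 by "applying multivariate analysis of variance (MANOVA) for repeated measures (within-between interactions) at the three time points".
- Primary outcome measure defines the bottom of the GAS scale: minus "2 indicates the participant’s current level of performance". Every participant therefore starts at −2 by construction.

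**The concern.** A model with time and group but no product of the two assumes that the arm difference is the same at every visit. It has one treatment coefficient and none that belongs to follow-up. Calling follow-up the primary endpoint in the same sentence does not create one.

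At stake is the meaning of the primary result. The averaged coefficient can be significant when the benefit has disappeared by 12 weeks, and it can miss a benefit that emerges only by 12 weeks. The sample size was worked out for a different term, the interaction, which the list does not contain. If the secondary outcomes use the same terms, they have the same problem.

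**Working it through.** **Reproducing the plan's figure.** Inputs from Sample size calculations: effect size 0.54, power 0.95, α 5%, three time points. There are two groups. For a repeated-measures MANOVA interaction, df1 = (2−1)(3−1) = 2, df2 = N−3 and λ = N × 0.54². The smallest N with power of at least 0.95 is 57 (power 0.953). The figure reproduces as a test of group × time with 0.54 entered as f(V). Whether 0.54 belongs in that place is a separate question. What matters here is that the term tested is an interaction.

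**What the listed model estimates.** With balanced data, the group coefficient in a random-intercept model without interaction is the plain mean of the visit-specific arm differences. The baseline difference is zero in expectation, because baseline precedes randomization, and exactly zero if all GAS scores are −2. With baseline rows included:

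coefficient = (0 + post-test difference + follow-up difference) / 3

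| Post-test effect | Follow-up effect | Group coefficient |
|---|---|---|
| 0.54 | 0.54 | 0.36 |
| 0.27 | 0.54 | 0.27 |
| 0.54 | 0 | 0.18 |
| 0 | 0.54 | 0.18 |
| 0.76 | 0 | 0.25 |

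Mixed models fitted to simulated trials of 90 gave 0.37, 0.25–0.27, 0.17–0.19 and 0.18–0.19 for the first four rows. With group × time added, the follow-up contrast averaged 0.53–0.56 when the truth was 0.54 and about 0 when it was 0.

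**How often the group term is significant.** Assumptions: 45 per arm, no dropout, unit SD at post-test and follow-up, baseline fixed at −2, and post-test/follow-up correlation ρ. The effects 0.54 and 0.76 are taken as standardised mean differences for illustration. The SD of a participant's mean over three visits is √[(2+2ρ)/9], and the standard error of the arm difference is that SD × √(2/45).

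At ρ = 0.6, SD = √(3.2/9) = 0.596 and SE = 0.126. For a 0.54 effect at one visit only, 0.18/0.126 = 1.43, which a two-sided 5% t test on 88 df declares significant in 29% of trials.

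| True effect (post-test, follow-up) | ρ = 0.3 | ρ = 0.6 | ρ = 0.8 |
|---|---|---|---|
| 0.54, 0 | 35% | 29% | 27% |
| 0.76, 0 | 60% | 51% | 47% |
| 0.54, 0.54 | 88% | 81% | 76% |

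A test of the follow-up difference alone rejects 5% of the time in the first two rows and about 72% in the third. The formula is symmetric in the two visits, so an effect of 0.54 at follow-up only is also detected in 29% of trials at ρ = 0.6, against 72% for a follow-up test.

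**Outcomes whose baseline varies.** With equal SDs and ρ = 0.6 between all visits, the SD of the three-visit mean is √[(1+2×0.6)/3] = 0.856. A sustained 0.54 effect is then detected in 51% of trials by the group term, against 72% by a follow-up comparison.

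**A trap in the obvious repair.** Suppose group × time is added but the baseline rows, the random intercept and a common residual variance are kept. The model then pools the visit variances: (0 + 1 + 1)/3 = 2/3 where the follow-up variance is 1. The follow-up standard error is too small by √(2/3) = 0.816, the effective critical value is 1.96 × 0.816 = 1.60, and the type I error is about 11% instead of 5%.

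**The case against.** The strongest reply is that a list of independent variables names variables and not every term. Group × time is built from two variables on the list, and nothing excludes it. The sample size section refers to exactly that interaction, follow-up is named as primary three times, and a journal article may leave coding of time and contrasts to an analysis plan. That much stands: the documents do not show that the authors meant to omit the interaction. They also do not say that the secondary models will carry identical terms.

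It does not remove the point. The article goes down to individual covariates and the random effect, and the list it gives conflicts with its own endpoint and its own sample size basis. That is a conflict between stated texts, not missing detail.

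A reader might infer that a one-third dilution means a one-third loss of power. For GAS it does not. A baseline fixed at −2 shrinks the coefficient and its standard error together, and for a sustained effect the averaged test is the more powerful one (81% against 72% at ρ = 0.6).

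It might also be said that baseline rows could be left out of the outcome. The wording about raw scores over nine months favours including them. If they were left out, a sustained effect would appear undiluted as 0.54, but the coefficient would average post-test and follow-up. The rejection rates for a faded benefit on GAS would not change, because coefficient and standard error both scale by 3/2.

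**Conclusion.** The point holds as a mismatch of estimand. The model as listed cannot deliver the 12-week follow-up effect declared primary, and it lacks the interaction on which the trial was sized. The 0.36 for a sustained 0.54 effect follows by arithmetic once baseline rows are included and data are balanced. The chance that a faded 0.54 benefit still makes the group term significant, 27–35%, rests on an assumed correlation of 0.3 to 0.8, complete loss of benefit by follow-up, 45 per arm and no dropout. The documents give no correlation or time course, and they allow for 37% attrition.

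A reader might go further and conclude that the trial will report a vanished benefit as success on its primary endpoint. The documents do not support that. It would require the analysts to fit no interaction, treat the averaged group term as decisive and present it as the 12-week result, and the text fixes none of these steps. The wording still needs correcting before analysis, because it determines what the primary result means.

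**What to change.** In Statistical analyses, state that time is a categorical factor, add group × time, and name the model-based KONTAKT minus Super Chef difference at the 12-week follow-up as the single primary test, with the post-test difference secondary.

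For GAS, either model only the post-test and follow-up scores or allow visit-specific variances through an unstructured covariance, so that the constant baseline does not shrink the follow-up standard error. Use the same follow-up contrast for the secondary outcomes, where baseline does vary. State in Sample size calculations how the interaction used there relates to this contrast.

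The cost is one or two lines of model wording. No new data or visits are needed.

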### Data collection

The data for this study will be collected by the measures as outlined in Table 3, at three time points, by an assessor blind to group allocation (1): before the intervention period (pre-intervention) (2); following the completion of the 16-week intervention (post-intervention); and (3), at 12 weeks following the intervention (follow up), with follow up being the primary endpoint. Additionally, there will be an 8-week data collection point for the cost analysis study (mid-intervention) (Table 3).

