### Secondary outcome measures

The Social Responsiveness Scale - Second Edition (SRS-2) standard version is a 65-item parent rating scale, designed to measure autistic-like traits in individuals aged 4–18 years. The SRS-2 enables calculation of a total score and five subscales: social awareness, social cognition, social communication, social motivation, and restricted interests and repetitive behaviour. The scale is scored on a 4-point Likert scale, ranging from “not true” (0) to “almost always true” (3). Scores range from 1 to 195 with the expected value for individuals with a primary diagnosis of ASD being approximately 100 [61]. Previous studies in individuals with ASD show good psychometric properties for SRS-2 (internal consistency of 0.9) [62, 63]. As recommended for research, the raw scores of the measure (total and subscale) will be used in this study [63].

The Circumplex Scale of Interpersonal Efficacy (CSIE) [64] measures an individual’s confidence in their ability to successfully perform behaviours associated with each facet of the interpersonal circumplex (assert, distance, yield, and connect). Each octant scale shows a progressive blend of two axial dimensions (e.g. “speak up” representing an assertive action, “get them to leave me alone” a distancing action, and “tell them when I am annoyed” combining these two actions) [65]. As suggested by previous research, this study will use these dimensional scores instead of the eight octants to predict the outcome [66]. Previous studies in adolescents with ASD have demonstrated acceptable internal consistency of 0.78 for this measure [64].

The Perth Aloneness Scale (PLS) is a self-report measure consisting of 24 statements such as “I feel left out of things at school”, or “I get along with my classmates”, measuring four dimensions of loneliness in young people (isolation, friendship, and positive and negative attitudes toward solitude) [67–69]. Responses are recorded on a 6-point Likert scale indicating agreement with a statement, ranging from “never” (1) to “always” (6), with higher scores suggesting higher levels of loneliness and negative attitude towards solitude. This scale has yielded good reliability for the overall scale and subscales (Cronbach’s alpha = 0.84). The use of the scale in the current study is further supported by established norms for Western Australian adolescents [67].

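### The primary GAS model adjusts for no entry measure of social functioning, and GAS's own baseline cannot supply one; prespecifying baseline SRS-2 would be a cheap gain in precision of unknown size

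*Protocol article*

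**What the plan says.** The Statistical analyses section of the protocol article plans a random effects regression with "raw data on the GAS scores (dependent variable") and a random effect for participant. The fixed effects are time, group, "age, IQ, gender, centre, and comorbidity as fixed effects, with follow up being the primary endpoint of the study". The list includes both stratification factors (gender and centre). It contains no SRS-2, ADOS-2 or other score of social functioning or autism severity.

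Under Primary outcome measure, a GAS score of −2 "indicates the participant’s current level of performance, −1 indicates less than expected", and 0 is the progress expected for that person. Every goal therefore starts at −2.

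Under Secondary outcome measures, SRS-2 is a parent rating "designed to measure autistic-like traits in individuals aged 4–18 years", and the article adds: "As recommended for research, the raw scores of the measure (total and subscale) will be used in this study". The Design section places the first data collection "at baseline, prior to randomization to intervention or control". The Data collection section says: "The data for this study will be collected by the measures as outlined in Table 3, at three time points". SRS-2 appears in the legend of Table 3, but the grid showing which measure falls at which visit is not available here.

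**The concern.** In most repeated-measures trials the baseline value of the outcome explains a good part of the later variation and absorbs chance differences between arms. GAS cannot do this, because its baseline has no variation between participants. The listed covariates are demographic, cognitive and diagnostic, so nothing in the model takes over that role.

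Two things are at stake. Outcome variance that a pre-randomisation score might explain stays in the error term. Part of any chance imbalance in entry social impairment also stays in the estimate. The Sample size calculations section itself expects GAS and the active control to limit power, and it responds only by recruiting more participants.

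**Working it through.** **1. The plan's own figure.** The sample size section works "Based on an effect size of 0.54", the average (0.76 + 0.32)/2. For a MANOVA within-between interaction with 2 groups, 3 time points, α = 5% and f(V) = 0.54, take df1 = 2, df2 = N − 3 and λ = N × 0.54². This gives N = 57 with power 0.953, matching the stated 57. Attrition: 1 − 57/90 = 36.7%, matching the stated 37%. The calculation assumes no covariate adjustment, so this point neither changes nor contradicts it.

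**2. What adjustment could gain.** Let r be the partial correlation of baseline SRS-2 with follow-up GAS, given age, IQ, gender, centre and comorbidity. The documents do not give r, so a range is assumed.

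- Residual variance removed: r².
- Equivalent sample size: 90/(1 − r²).
- Power, for illustration only: two-sided 5% t-test (noncentral t), with 0.54 read as a standardised mean difference and enlarged to 0.54/√(1 − r²). This uses 45 per arm (N = 90), or 57 completers if the full attrition allowance is used.

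| r | Variance removed | Equivalent N | Power, N = 90 | Power, 57 completers |
|---|---|---|---|---|
| 0 | 0% | 90 | 0.717 | 0.52 |
| 0.1 | 1% | 90.9 | 0.721 | 0.52 |
| 0.2 | 4% | 93.8 | 0.734 | 0.53 |
| 0.3 | 9% | 98.9 | 0.757 | 0.56 |
| 0.5 | 25% | 120 | 0.833 | 0.64 |

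The 0.717 in the first row should not be set against the planned 0.95. The plan's figure enters 0.54 as f(V), while the table reads it as a standardised difference. Which reading is right is a separate question. Only the change down each column matters here.

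**3. Chance imbalance.** The difference in mean baseline SRS-2 between arms of 45 has standard error √(2/45) = 0.21 SD. Only r times an imbalance reaches the GAS contrast. A one-standard-error imbalance therefore shifts it by:

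- r = 0.1: 0.02 SD, about 4% of 0.54.
- r = 0.3: 0.06 SD, about 12%.
- r = 0.5: 0.11 SD, about 20%.

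**4. How the covariate must enter.** Suppose the constant baseline rows are kept and the effect at follow-up is read from a group-by-time term. With complete data that term equals the difference between arms in mean change from baseline to follow-up. A covariate entered only as a main effect adds the same amount to every visit of a participant, so it cancels from that person's change. The group-by-time estimate is then the same with and without it.

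If SRS-2 is allowed a different slope at each visit, or if only post-baseline GAS is modelled, it does act on the follow-up contrast. With unit SD and 45 per arm, the standard error then falls from √(2/45) = 0.211 to 0.211 × √(1 − r²), which is 0.183 at r = 0.5.

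A simulation at r = 0.5 showed the same pattern. The SD of the follow-up estimate was 0.196 both with and without a plain SRS-2 main effect, and about 0.163 with an SRS-2-by-time term or a post-baseline-only model. The absolute values depend on the variances simulated; the pattern does not.

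**The case against.** The strongest reply is that this is an optional refinement. The model is prespecified, includes both stratification factors and gives a valid comparison without SRS-2. Chance variation in SRS-2 is already reflected in the standard error. That stands: a reader might infer that the omission biases the treatment effect, but under randomisation it does not.

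A second reply is that r may be low, for reasons found in the article. Goals are anchored to each adolescent's own level and expected progress, which weakens dependence on entry severity. GAS is self-rated (Abstract), whereas SRS-2 is a parent report. The Background stresses how far adolescent and parent ratings of emotional and social functioning diverge. The listed covariates may also already carry part of what SRS-2 would add. This stands too. The larger gains in the table need r = 0.5, and nothing in the documents supports expecting that value.

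A third reply is that SRS-2 is one candidate among several. It covers restricted and repetitive behaviour as well as social traits, and ADOS-2, ERSSQ and CSIE are also listed. That is fair. SRS-2 is a reasonable choice because it was the primary outcome of the earlier Swedish trials and the source of the effect size used here, but that does not show that it predicts GAS.

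These replies limit the size of the point. They do not remove it, because the covariate list is stated in the article and the remedy costs almost nothing.

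**Conclusion.** The point holds as a minor to moderate improvement in efficiency. The primary model contains no entry measure of social functioning, and baseline GAS is constant, so it cannot act as one. The gain from baseline SRS-2 is negligible below a partial correlation of about 0.2. At 0.3 it is about 9% of residual variance (about 9 participants at N = 90), and at 0.5 it is 25% (about 30 participants).

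Three stronger readings are not supported. The first is that an imbalance in SRS-2 carries over in full to the primary contrast; only the fraction r does. The second is that the trial forgoes a known amount of power; r is not reported and may be small. The third is that simply adding SRS-2 to the list of fixed effects is enough; with the constant baseline rows kept, a main effect alone leaves the group-by-time contrast unchanged.

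The conclusion assumes that SRS-2 is collected before randomisation. That is inferred from the Design and Data collection sections and the Table 3 legend. Nothing in the text contradicts it.

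**What to change.** In the Statistical analyses section, name baseline SRS-2 raw total score as a covariate of the primary GAS model, chosen before unblinding and kept whatever its p-value. State how it enters, in one of two ways:

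- model post-baseline GAS only (post-intervention and follow-up), with baseline SRS-2 as a covariate; or
- if the constant baseline rows are kept, include an SRS-2-by-time term.

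Confirm from the Table 3 grid that SRS-2 is taken at baseline, and state a rule for the few participants whose baseline value is missing.

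No new data are needed. The cost is one degree of freedom for a single slope over the post-baseline visits, or two if the slope differs by visit. With about 10 model parameters, one degree of freedom is repaid once r exceeds roughly √(1/80) = 0.11 at N = 90, or √(1/47) = 0.15 with 57 completers. Naming the covariate now also avoids the appearance of a data-driven choice, which would arise if it were added after an imbalance had been seen.
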